**Objective**

- **To determine the safety and tolerability of multi-doses of Orameds oral insulin in people with type 1 diabetes**

Secondary Outcome Measures:

**To determine if oral insulin is likely to improve glycemic stability assessed by the reduction of the frequency and severity of hypoglycemic episodes in people with unstable type 1 diabetes**

**Diabetes** has emerged as a primary health threat of the 21st century. The condition formally termed *diabetes mellitus* is a hormone disorder signified by the cells’ inability to absorb glucose from the blood. This can occur either when there is not enough insulin in the blood, or when the body’s cells fail to respond normally to the insulin that is present. In either case, the negative results are manifold: First, the blood becomes flooded by an overabundance of sugar, sending glucose concentrations in the blood shooting up to dangerous levels. Second, without insulin, muscle and liver cells cannot absorb glucose from the blood, so these cells lack sufficient sugar and are therefore starved for energy. As a result, the body’s supply of fats and proteins must be consumed for “fuel” to keep normal physiologically processes going, simultaneously both depleting the body’s energy storages and disrupting normal metabolic regulation of fats and proteins.

Hypoglycemia is prevalent in diabetes. The DCCT reported a threefold increasein severe hypoglycemia and coma in intensively treated patientsas compared to conventionally treated patients. An intensively treatedindividual with type 1 diabetes can experience up to 10 episodesof symptomatic hypoglycemia per week and severe temporarilydisabling hypoglycemia at least once a year. An estimated2-4% of deaths of people with type 1 diabetes have been attributedto hypoglycemia. Hypoglycemia is less common and generally less severe intype 2 diabetes, but is not uncommon in clinicaltrials using insulin to achieve good metabolic control.

Hypoglycemia can cause severe physical and/or psychosocial morbidity and sometimes death, depending on its severity or duration. Central nervous system glucosedeprivation (neuroglycopenia) is of major concern as it can lead to irreversible brain damage and result in cognitive impairment, seizure disorder and emotional lability. Moreover, the fear and concern of hypoglycemia often precludes tight glycemiccontrol and limits full realization of glycemic control’slong-term benefits in preventing diabetes associated complications inthe vast majority of patients. Hypoglycemia is often the cause of autonomic dysfunction and thus the more episodes of hypoglycemia a patient has, the more the body’s glucoregulatory response is blunted, decreasing the patient’s awareness of a pending hypoglycemic episode (hypoglycemia unawareness). The concept of hypoglycemia-associatedautonomic failure in diabetes posits that recent antecedent hypoglycemia causes both defective glucose counter regulation and hypoglycemia unawareness so that antecedent hypoglycemia leads to a vicious cycle of recurrent hypoglycemia and further impairment of glucose counter regulation. Put in other words, the more episodes of hypoglycemia a patient has, the more the body’s response is blunted, decreasing the patient’s awareness of an episode.Insulin excess due either to endogenous secretion or to exogenous doses appears to be the most consistent cause of hypoglycemia and iatrogenic hypoglycemia is the most common scenario. However, other factors such as dietary intake, physical activity, alcohol use, and drug interactions also may increase the risk of hypoglycemia. Furthermore, recent studies strongly suggest that abnormalities in glucose counter regulation are important—and perhaps dominant—factors in the development of severe hypoglycemia.

Among insulin dependent diabetic subjects there is a subgroup of individuals who exhibit swings of extremes of hyperglycemia to hypoglycemia for no obvious reason. Such patients are defined as having the syndrome of “unstable” or brittle diabetes and they tendto defy all attempts at orthodox glycemic control and the conditiondisrupts the lives of themselves, their relatives and their healthcare teams, recurrentand long hospital admissions are the rule. The peak age-groupfor brittle “unstable” diabetes is 15-30, but it can occur in older patients as well as in younger individuals. Suggested causes included subcutaneous insulin degradation, impaired hyperemic responses to insulin injection, and enhanced insulin clearance. Presently, it is believed that "Pure" recurrent hypoglycemia is associated with loss of awareness of low glucose concentration. The syndrome of recurrent severe and asymptomatic hypoglycemia, associated with delayed adrenergic and autonomic counterregulatory responses, has been recognized in patients receiving intensified insulin treatment and may result from rather than be the initiating cause of recurrent hypoglycemia. The vicious circle that results, however, makes it particularly dangerous for these patients as it is reported to be a cause of mortality amongst them.

The normal counter regulatory responses to hypoglycemia is basically as follows; a decrease in plasma glucose normally triggers a cascade of reactions, mostly hormonal, that rapidly return the glucose concentration to baseline levels. Ultimately there is an increase in glucose production in the liver (and kidneys) and a decrease in peripheral glucose utilization. Both mechanisms act in opposition to the effects of insulin and, hence, result in the reversal of hypoglycemia.

Different counter regulatory mechanisms are activated at different threshold levels of glucose concentration. The first defense against a falling plasma glucose concentration is a decrease in endogenous insulin secretion. This mechanism is critical in patients with residual endogenous insulin secretion. Of the other hormones, epinephrineand glucagonappear to be the most potent counter regulatory factors and are the primary fast-acting hormonesin the defense against acute hypoglycemia. These hormones are secreted promptly after plasma glucose levels fall, and both induce a rapid increase in endogenous glucose production. Glucagon acts toincrease endogenous glucose production and does so via increasesin hepatic glycogenolysis and gluconeogenesis, providing threecarbon glucose substrates (lactate, pyruvate, alanine, and glycerol).Epinephrine can also acutely increase endogenous glucose production.Epinephrine has effects similar to glucagon on hepatic glucoseproduction but can also stimulate net renal glucose production. Additionally,epinephrine has an important physiological function in reducing insulin-stimulatedglucose uptake. Other major counter regulatory hormones seem to be less critical in the initial phase of a hypoglycemic episode but are important in the later stage of glucose stabilization. Cortisoland growth hormoneboth help the liver to sustain glucose output in the face of hyperinsulinemia. In addition, these hormones reduce peripheral glucose use during recovery from hypoglycemia, an action shared by epinephrine.

An appropriate increase in endogenous glucose production (EGP)is critical for the recovery from **hypoglycemia. B**oth Glucagon and epinephrine act toincrease endogenous glucose production via increasesin hepatic glycogenolysis and gluconeogenesis, the two majorsources of glucose-6-phosphate destined for dephosphorylationand glucose release. Glycogenesis and glycogenolysis take placesimultaneously, with the preponderance favoring glycogenolysiswhen an increase in EGP is required, whereas gluconeogenesisis favored in the fasting, postabsorptive state. Recent studies suggest that glycogenbreakdown may be the primary mechanism responsible for the increasein EGP during the initial recovery from insulin-induced hypoglycemia,followed by an increase in gluconeogenesis.

Type 1 diabetic subjects have an impaired hepatic glycogen metabolism characterized by reduced glycogen content, glycogen being the principal short-term reserve for circulatingglucose. Patients with poorly controlled type 1 diabetesaccumulate poor hepatic glycogen stores during feeding and consequently they sustain limited rates of endogenous glucose productionduring fasting. The maintenance of fasting euglycemiain response to a drop in blood glucose levels becomes more dependenton the activation of gluconeogenesis by counter regulatory mechanisms than on glycogen breakdown.For many type 1 diabetic subjects this defect increases their vulnerability to a hypoglycemicepisode, particularly fasting hypoglycemia

Glycogen synthesis is regulated by portal vein concentrations of insulin and glucagon. The normalization of hepatic glycogen metabolismin type 1 diabetic patients can only be achieved by increasedportal vein insulin (insulin/glucagon ratio) that favors glycogen synthesis which stimulates glycogen synthesis flux, inhibits glycogen phosphorylase flux to result in suppression in the rate of hepatic glycogen cycling and an increase in the rate of net hepatic glycogen synthesis.

A shift in insulin to glucagon ratio (in favor of glycogenesis) in the portal vein can be achieved either by systemic administration of insulin (parenteral administration) or by administering insulin orally (insulin that is ferried directly to the portal vein). Because of the natural gradient 3:1 gradient of portal/peripheral concentration of insulin, administering insulin systemically is likely to require large amounts of insulin which are likely to place the individual at risk for hypoglycemia. In contrast, oral insulin administration restores (albeit temporarily) the high portal insulin levels required for glycogenesis with no systemic hyperinsulinemia (minimal amounts of insulin spills over to the periphery) and is thus devoid of the risk of hypoglycemia.

Oramed Pharmaceuticals inc. has developed an oral insulin dosage form which has undergone extensive preclinical and clinical evaluation and is currently in phase 2 clinical trials. Clinical results up until now have demonstrated that oral insulin administration is safe and well tolerated by healthy individuals as well as by people with type 1 and type 2 diabetes. Orameds’ oral insulin is absorbed from the gastrointestinal tract to result in consistent reduction in blood glucose, reduction in c-peptide and does not cause hypoglycemia.

The intent of this proposed study is to assess the potential of oral insulin to mitigate diabetic instability and reduce the frequency and severity of hypoglycemic episodes in patients with type 1 diabetes. Restoring hepatic glycogen stores is critical for the normalization of conterregulation to hypoglycemia in these patients. Oral insulin can provide a means to increase portal insulin levels, shift the ratio of insulin/glucagon in favor of glycogenesis while sparing the patient the risk of hypoglycemia due to peripheral hyperinsulimia.

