**Study Design**:

- The patient will be screened and an informed consent be obtained. A total of 8-12 type 1 diabetic patients with known uncontrolled type 1 diabetes will be recruited into this study at one investigational site. Patients will remain on their current medication with no changes to dose or regimen. Patients will undergo 5 days of run-in period whereby data from the CGM will be collected to assess the glycemic swings. The data will serve as a base-line for comparison. After the 5 day run-in period patients will be administered oral insulin for duration of 10 days. Oral insulin will be administered in one capsule given 45 min. before each meal. (The intervals of 5, and 10 days were chosen based on the life of the sensor- The average sensor lif3e is 5 days at which point it needs to be changed).
- Hypoglycemic episodes will be assed by clinical reporting and by Continuous glucose monitoring (CGMS). CGMS consists of a sterile disposable subcutaneous glucose-sensing device connected by a cable to a glucose monitor. The system allows downloading and reviewing of the data on a personal computer. The sensing device (needle) detects glucose levels in the subcutaneous interstitial fluid electrochemically (reaction with glucose oxydase) and registers it at frequent intervals, the data collected is stored and will be analyzed at the completion of the study.
- Hypoglycemia severity grading: Mild (grade 1) - Patient is aware of, responds to and self-treats the hypoglycemia Moderate (grade 2) -Patient cannot respond to hypoglycemia and requires help from someone else, but oral treatment is successful, Severe (grade 3) - Patient is semi-conscious or unconscious or in coma ± convulsions and may require parenteral therapy (glucagon or IV glucose)

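### Glycemic stability is judged by hypoglycemic episodes alone, so a rise in mean glucose with unchanged swings could be read as better stability

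*Protocol*

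**What the plan says.** The secondary outcome, under Objective in the protocol, reads: "To determine if oral insulin is likely to improve glycemic stability assessed by the reduction of the frequency and severity of hypoglycemic episodes". The target group is patients whose type 1 diabetes is unstable. This names a broad concept, stability, and fixes how it is to be judged.

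The background text under the same heading says what unstable means. It describes "a subgroup of individuals who exhibit swings of extremes of hyperglycemia to hypoglycemia for no obvious reason" and continues: "Such patients are defined as having the syndrome of “unstable” or brittle diabetes". Later it gives the study's intent as "to mitigate diabetic instability and reduce the frequency and severity of hypoglycemic episodes in patients with type 1 diabetes", which sets instability and hypoglycemia side by side as two aims.

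Study Design says of the five-day run-in: "data from the CGM will be collected to assess the glycemic swings. The data will serve as a base-line for comparison". It then says that hypoglycemic episodes are ascertained by clinical reporting and by CGM, and it gives a three-grade severity scale for hypoglycemia. There is no corresponding measure of hyperglycemia, mean glucose or variability. According to Treatment Phase, CGM continues through the ten treatment days.

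**The concern.** The concept has two sides and the measure has one. The protocol's account of instability covers excursions to high and to low glucose, while the declared outcome counts and grades only the low ones. The run-in is announced as a record of swings, but no swing quantity reappears in the outcome that is meant to judge stability.

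This matters because the frequency of hypoglycemia depends on the level of glucose as well as on its spread. If the whole profile moves up with its spread unchanged, low readings become rarer and high readings more common. The declared outcome would score that as improved stability. The study compares treatment with run-in in the same patients and has no concurrent control, so it could not tell a shift with another cause, such as changed eating while wearing a monitor, from an effect of the capsule. At stake is the study's one efficacy conclusion. The primary safety objective is not affected.

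**Working it through.** **Plan's own figure.** There is none to reproduce. The protocol states no effect size, SD, event rate or glucose threshold for this outcome. The argument rests on the text; the arithmetic only illustrates its size.

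**Text side by side.**
- Meaning of unstable (background under Objective): swings between hyperglycemia and hypoglycemia.
- Intent (same section): instability and hypoglycemia, joined as two aims.
- Run-in CGM (Study Design): swings, serving as baseline, with no metric named.
- Declared stability outcome (Secondary Outcome Measures): hypoglycemic episodes, frequency and severity.

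The last entry replaces the first with one half of it.

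**Illustration: inputs, all assumed and none from the documents.** CGM glucose is normal with mean m = 170-200 and SD s = 60-80 mg/dL; low glucose is below 70 mg/dL; the mean rises by d = 10 or 20 mg/dL with s unchanged. Time below 70 stands in for episodes.

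Formula: P(below 70) = Φ((70 − m − d)/s). Relative cut = 1 − P(with shift)/P(without shift).

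The corners that set the range are:
- m = 170, s = 80: Φ(−1.250) = 10.57%; with +10, Φ(−1.375) = 8.46%; with +20, Φ(−1.500) = 6.68%. Cuts: 20% and 37%.
- m = 200, s = 60: Φ(−2.167) = 1.51%; with +10, Φ(−2.333) = 0.98%; with +20, Φ(−2.500) = 0.62%. Cuts: 35% and 59%.

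Over the whole grid the cut is therefore about 20-35% for +10 and 37-59% for +20. A log-normal shape at constant CV gives about 25-46% and 43-71%.

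**The other side of the range.** At m = 180, s = 70, with s unchanged:

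| Rise in mean (mg/dL) | Below 70 | 70-180 | Above 250 |
|---|---|---|---|
| 0 | 5.8% | 44.2% | 15.9% |
| +10 | 4.3% | 40.0% | 19.6% |
| +20 | 3.2% | 35.6% | 23.8% |

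**Episodes instead of time.** Simulated autocorrelated five-day traces with the same mean and SD, counting runs below 70 of at least 15 minutes, gave 4.87 episodes per five days with no shift, 3.80 with +10 and 2.92 with +20. The cuts are 1 − 3.80/4.87 = 22% and 1 − 2.92/4.87 = 40%. The count of episodes moves in the same way as time below 70, with the SD fixed at 70 throughout.

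**The case against.** Four points can be made for the plan.

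*An upward shift is unlikely.* Study Design keeps current medication unchanged in dose and regimen, and the study adds insulin, so the direct effect would be expected to lower glucose. This stands. A shift is a possible artefact, not a predicted one, and a cut in injected insulin would be a departure from the protocol and should not be offered as the cause. Food intake is not described as controlled, however, and the background text itself lists diet and physical activity among the factors that influence hypoglycemia. The mismatch of definition remains whatever the cause of a shift.

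*Swings are in fact recorded.* This also stands. A reader might infer that baseline and outcome are different quantities, or that hyperglycemia is never looked at. The documents do not support either. CGM runs in both periods and also captures hypoglycemic episodes, so a like-for-like episode baseline exists, and the run-in data are expressly collected to look at swings. The fault is narrower: no swing measure enters the stability judgement.

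*The choice of CGM summary belongs in the SAP, which is not shown.* That would answer a silent protocol. This one is not silent: it states how stability is assessed, and an SAP that follows it inherits the one-sided rule.

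*Hypoglycemia is the study's rationale, and this is a secondary aim in 8-12 patients.* That is fair, and it is why renaming the outcome is an acceptable remedy. It does not justify keeping the word stability for a count of low-glucose events.

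**Conclusion.** The point holds as a mismatch between a concept and its measure. The protocol describes instability as two-sided and judges stability by hypoglycemic episodes alone, so a fall in episodes would not by itself show that stability improved.

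The direction is the same under every assumption tried. The size depends on the assumed mean, SD and shape, none of which is in the documents: about 20-35% less time below 70 mg/dL for a 10 mg/dL rise and 37-59% for a 20 mg/dL rise (normal), or 25-46% and 43-71% (log-normal). Time below 70 is only a proxy. The protocol's severity grades rest on awareness, need for help and consciousness, and the illustration says nothing about them.

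The result does not show that glucose will rise in this study, or that a fall in hypoglycemia would be of no value. It shows that the outcome cannot separate less variability from a higher level.

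**What to change.** In Secondary Outcome Measures, do one of the following.

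1. Name a CGM variability measure, such as SD or CV, as the stability outcome, computed in the same way in run-in and treatment. Keep frequency and severity of hypoglycemic episodes as a separate outcome. Report mean glucose and time below, in and above range beside both. The mean is needed for interpretation because the two measures respond differently to a shift: at a fixed SD of 70, a move of the mean from 180 to 200 leaves the SD unchanged but lowers the CV from 70/180 = 38.9% to 70/200 = 35.0%.
2. Rename the outcome as reduction in hypoglycemia and drop the stability claim, with mean glucose reported beside it.

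A rule that every measure must improve with no rise at all in mean glucose or time above range is not needed. Without a tolerance, chance alone could fail it in 8-12 patients.

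The cost is a change of wording and a little more analysis of CGM data already planned. No visit, device, participant or treatment rule changes.

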**Proposed Mechanism:**

Any attempt to develop an oral insulin modality must take into account two major obstacles that result from insulin’s biochemical character as a polypeptide: 1) Its direct transfer across the mucosal barrier is restricted; 2) it is subject to degradation by the proteolytic enzymes located in the stomach and intestinal lumen.

To overcome these barriers, our proposed mechanism utilizes several co-factors to prevent the digestion of the introduced hormone in the gastrointestinal tract and to facilitate its physiological absorption. After performance of a range of studies for optimization of co-factors, we have identified the most efficacious formulation of encapsulated oral insulin. The proposed composition contains: (1) crystalline insulin, (2) a digestion enhancer, and (3) a formula protector, (4) Omega 3-rich fish oil, in a coated capsule. These components are expanded upon in greater detail below. Each has a target function which promotes the goals of our treatment modality. The enhancer functions as an effective enhancer of the mixture. The protectors prevent enzymatic degradation of the insulin by mucosal enzymes.

.

**Study Design**:

- The patient will be screened and an informed consent be obtained. A total of 8-12 type 1 diabetic patients with known uncontrolled type 1 diabetes will be recruited into this study at one investigational site. Patients will remain on their current medication with no changes to dose or regimen. Patients will undergo 5 days of run-in period whereby data from the CGM will be collected to assess the glycemic swings. The data will serve as a base-line for comparison. After the 5 day run-in period patients will be administered oral insulin for duration of 10 days. Oral insulin will be administered in one capsule given 45 min. before each meal. (The intervals of 5, and 10 days were chosen based on the life of the sensor- The average sensor lif3e is 5 days at which point it needs to be changed).
- Hypoglycemic episodes will be assed by clinical reporting and by Continuous glucose monitoring (CGMS). CGMS consists of a sterile disposable subcutaneous glucose-sensing device connected by a cable to a glucose monitor. The system allows downloading and reviewing of the data on a personal computer. The sensing device (needle) detects glucose levels in the subcutaneous interstitial fluid electrochemically (reaction with glucose oxydase) and registers it at frequent intervals, the data collected is stored and will be analyzed at the completion of the study.
- Hypoglycemia severity grading: Mild (grade 1) - Patient is aware of, responds to and self-treats the hypoglycemia Moderate (grade 2) -Patient cannot respond to hypoglycemia and requires help from someone else, but oral treatment is successful, Severe (grade 3) - Patient is semi-conscious or unconscious or in coma ± convulsions and may require parenteral therapy (glucagon or IV glucose)

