**END OF STUDY/EARLY DISCONTINUATION:**

After completion of Period 2, subjects will complete the following end of study evaluations:

- Vital signs (blood pressure, heart rate) will be measured in the sitting position after at least 5 minutes of rest.
- Clinical laboratory evaluations (hematology, chemistry)
- Physical Exam

Subjects who are discontinued early from the study will complete the end of study evaluations at the time of early discontinuation.

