**TREATMENT REGIMEN**:

The treatment regimen is as follows:

1. Period 1: no added medication. 5 days CGM. No change in current treatment.
2. Period 2: For 10 days one capsule of insulin before each meal (3 time/day). Each capsule contains: 8 mg insulin.

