**SAFETY EVALUATIONS:**

- Adverse events will be collected throughout the study beginning from the time the subject signs the consent form until the end of study evaluations
- Concomitant medications/therapies will be recorded throughout the duration of study, beginning from the time the subject signs the informed consent.
- Vital signs (blood pressure, heart rate) will be measured in the sitting position after at least 5 minutes of rest at the following times:
- Screening
- At the end of period 1
- End of study
- Clinical laboratory evaluations (chemistry, hematology) will be performed at screening and at end of study or early discontinuation. .
- Physical examinations at screening and end of study or early discontinuation.

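### Background insulin is held fixed with no safety exception, and no action follows the grade 2 or 3 hypoglycemia that the protocol defines (minor, cheap to fix)

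*Protocol*

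**What the plan says.** Study Design sets the background rule: "Patients will remain on their current medication with no changes to dose or regimen". The sentence precedes the description of both periods and carries no exception. Treatment Regimen repeats the rule for Period 1 and adds the study drug in Period 2: "For 10 days one capsule of insulin before each meal (3 time/day", each capsule holding 8 mg.

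Study Design also grades hypoglycemia. Grade 2 is defined by "Patient cannot respond to hypoglycemia and requires help from someone else", with oral treatment succeeding. Grade 3 is defined by "Patient is semi-conscious or unconscious or in coma", with or without convulsions and with possible parenteral treatment. These treatments serve to define the grades. They are not followed by any instruction about background insulin or capsules.

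Three other provisions bear on the point:

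- End of Study/Early Discontinuation: "Subjects who are discontinued early from the study will complete the end of study evaluations at the time of early discontinuation". No criterion for discontinuing is given.
- Safety Evaluations: "Concomitant medications/therapies will be recorded throughout the duration of study". Adverse events are collected over the same span.
- Exclusion Criteria (under Sample Size): patients who live alone are excluded for lack of family support.

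**The concern.** The first objective is safety and tolerability of repeated doses, in patients described as having uncontrolled type 1 diabetes. If one of them has a grade 2 or 3 event and remains in the study, a literal reading leaves the background insulin where it was and the capsules running. The moment at which a clinician would most want to review the dose is covered by a rule that allows no change.

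The protocol's own background, under Objective, shows why dose matters: "Insulin excess due either to endogenous secretion or to exogenous doses appears to be the most consistent cause of hypoglycemia". It also describes a concept of autonomic failure in which "antecedent hypoglycemia leads to a vicious cycle of recurrent hypoglycemia and further impairment of glucose counter regulation". An investigator who lowers insulin anyway is outside the written rule. One who follows the rule must choose between an unchanged dose and losing the patient.

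This is not a matter for the statistical analysis plan. Background dosing and study-drug holds are instructions to the site, and the point rests on a rule that the protocol states without qualification.

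**Working it through.** There is no figure in the protocol to reproduce. The check is mainly textual, with a little arithmetic for scale.

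**1. What each section allows after a grade 2 or 3 event**

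| Section | What it provides | Does it settle dosing afterwards? |
|---|---|---|
| Study Design (background rule) | No change in dose or regimen | Yes, by fixing the dose |
| Study Design (grades) | Names the acute treatment for each grade | No |
| Study Design (CGM) | Data stored and analysed once the study is complete | No |
| Treatment Regimen | Fixed capsule schedule, no hold | No |
| Study Duration; End of Study/Early Discontinuation | Patient can leave; evaluations listed | Only by withdrawal |
| Safety Evaluations | Adverse events and concomitant therapies recorded | No |
| Exclusion Criteria | No patients who live alone | No; it helps during an episode |

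For a patient who stays in, no section permits a reduction in background insulin or a pause in capsules. Safety Evaluations also schedules no vital signs, laboratory tests or examination between the end of Period 1 and the end of study or early discontinuation, so no planned visit fills the gap.

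**2. Cost of the withdrawal route.** With 8 to 12 patients (Study Design), one withdrawal is 1/8 = 12.5% or 1/12 = 8.3% of the sample.

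**3. Exposure under the schedule.** 3 × 8 mg = 24 mg per day; × 10 days = 240 mg in 30 capsules. Capsules still planned after an event at the end of day d number 3 × (10 − d): 27 for d = 1 and 15 for d = 5. These counts describe the schedule. They do not measure harm, and they say nothing about the background insulin.

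**4. Could such an event occur in the trial?** The protocol gives no rate for these patients. Its background text says that intensively treated type 1 patients can have severe hypoglycemia at least once a year. *Assuming* r events per patient-year, a Poisson count and no effect of the capsule:

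expected events = n × (10/365) × r; P(at least one) = 1 − exp(−expected)

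| r (assumed) | n = 8: expected, P | n = 12: expected, P |
|---|---|---|
| 1 | 0.22, 20% | 0.33, 28% |
| 2 | 0.44, 36% | 0.66, 48% |
| 5 | 1.10, 67% | 1.64, 81% |

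This shows only that the situation is plausible. It is not an estimate for this trial.

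**5. What a hold or stop would cost.** Planned treatment days are 8 × 10 = 80 to 12 × 10 = 120. A hold of one day in one patient, taken as an illustration, is 1/80 = 1.25% to 1/120 = 0.83%. Stopping one patient at the end of day 5 loses 5/80 = 6.25% to 5/120 = 4.2%.

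**6. Direction of bias if background insulin is lowered.** The secondary outcome compares hypoglycemia on treatment with a 5-day run-in, with no control arm. A reduction in Period 2 would tend to lower later hypoglycemia and so favour the capsule. A reduction during run-in would alter the baseline.

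**The case against.** The strongest reply is that the protocol is safer than the concern suggests, and that the fixed regimen has a purpose.

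- **A safe, compliant route exists.** The investigator can withdraw the patient. This stands, and it is the main reason why the point is minor.
- **Rescue is not barred.** A reader might infer that the protocol forbids treating an episode. It does not: the grade definitions themselves name oral treatment, glucagon and IV glucose, and excluding patients who live alone supports help from another person.
- **The no-change sentence describes the design and does not address emergencies.** It never defines a deviation, and any change would be captured as concomitant therapy. A lenient reading is possible. But the sentence is unqualified, and recording a change is not the same as permitting it.
- **Constant background insulin protects the comparison.** This stands. In an uncontrolled before-after study it is a real cost of any exception, so the fix must deal with the affected data.
- **The background text is broader than insulin excess.** It also says that abnormal counter-regulation may be the dominant factor in severe hypoglycemia. So the text does not show that lowering insulin would prevent every severe event. A reader might also infer that a single episode starts a cycle of recurrence. The text says only that a concept posits this for recent antecedent hypoglycemia.
- **The protocol says that the oral insulin does not cause hypoglycemia.** That may explain the omission, but the statement does not cover the background insulin, and the safety of repeated dosing is what the trial sets out to determine.

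**Conclusion.** The point holds as a minor, cheap improvement. Background medication is fixed without a safety exception while insulin is added, and no action on background insulin or capsules follows a grade 2 or 3 event. On a literal reading, a patient who stays in after a severe event has no protocol-compliant way to have background insulin reduced, and nothing pauses the capsules.

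Its size is limited. The alternative that the protocol leaves open costs 8.3% to 12.5% of the sample per patient withdrawn. No harm is quantified, because the event rate in these patients is not given. A reader might infer that the plan exposes patients to a demonstrable excess of severe events, or leaves the investigator no safe option. The document supports neither inference: it gives no such rate, and early discontinuation is always available.

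The conclusion rests on taking the no-change sentence as written, for both periods.

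**What to change.** 1. Add to Study Design: *Background insulin may be reduced when the investigator judges this necessary for safety after a grade 2 or 3 event; the date, the dose change and the reason are recorded.*
2. Add to Treatment Regimen: *After a grade 3 event in the treatment phase, capsules are held until the investigator has reviewed the patient and recorded a decision to continue or stop. After a grade 2 event the investigator reviews the patient and records the same decision.*
3. Add a data-handling sentence, in the protocol or the analysis plan: *CGM and hypoglycemia data after any change in background insulin are flagged, and the run-in versus treatment comparison is reported with and without those days.*

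Both triggers are clinical grades, so they work although the stored CGM data are analysed only at the end.

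**Cost.** A short amendment. Concomitant therapies are already recorded, so the new items are the reason for a change, the capsule decision and the data flag. A few treatment days may be lost to holds or stops. The main downside is the bias shown in step 6. The third addition makes it visible but does not remove it, because leaving out flagged days removes them selectively, after an event.
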